# Deferring Postoperative Follow‑Up Visits up to 4 Weeks After Uneventful Cataract Surgery in a Tertiary Level Eye Hospital: Protocol for a Prospective, Quantitative, Experimental Control Study

**DOI:** 10.2196/48616

**Published:** 2023-08-31

**Keywords:** cataract surgery, operational research, SICS, small-incision cataract surgery, postoperative visits, cataract, follow-up visit, postoperative care, surgery

## Abstract

**Background:**

Routine examination after cataract surgery, including a refraction test 4 to 6 weeks after surgery, is mandatory in most hospitals. In recent years, there has been growing interest in exploring alternative approaches to postoperative follow-up in cataract surgery patients due to the increasing number of cataract surgeries being performed, the limited availability of health care resources, and the need to optimize the use of health care services.

**Objective:**

We aim to compare postoperative visual outcomes after a day 0 examination in patients with 2 follow‑ups, one on day 7 and other on day 30, and patients with a single ophthalmic follow‑up between days 25 to 30.

**Methods:**

A prospective, quantitative, experimental control study will be carried out in Reiyukai Eiko Masunaga Eye Hospital, located in Banepa, Kavrepalanchok, Nepal. All patients undergoing cataract surgery meeting the inclusion and exclusion criteria irrespective of the type of surgery (small-incision cataract surgery or phacoemulsification) will be included in the study. The patients will be randomly assigned to 1 of 2 groups. Patients in group 1 will be examined on day 1, day 7, and day 30, whereas patients in group 2 will be examined on day 1 and once between days 25 to 30. The minimum clinically important difference (MCID) in our study will be set according to the improvement in the Snellen visual acuity chart.

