### Specific Objectives

The specific objectives are (1) to compare postoperative visual outcomes after a day 0 examination in patients with either 2 follow‑up visits, one on day 7 and the other on day 30, or 1 ophthalmic follow‑up visit between day 25 and day 30; (2) to assess the safety of deferring the first follow‑up visit at 1 week; and (3) to perform a cost-benefit analysis of the intervention.

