## Methods

### Study Design, Setting, and Participants

This will be a prospective, quantitative, experimental, noninferiority control study of health services use. Selected patients undergoing cataract surgery at Reiyukai Eiko Masunaga Eye Hospital irrespective of the type of surgery (SICS or phacoemulsification) will be included in the study.

All enrolled patients will undergo an examination on the first postoperative day conducted by an ophthalmologist who is unaware of the patient’s group assignment. Subsequently, the patient will proceed to the counselor’s office, where a unique identification number will be generated and the patient will be randomized into either group 1 or group 2.

In group 1, patients will be instructed to attend follow-up visits at 1 week and 1 month postoperatively. In group 2, patients will be instructed to attend a follow-up visit at 1 month postoperatively only. During the visit, the patients will receive detailed guidance on the appropriate use of medications and be educated about the signs and symptoms they should be vigilant for. The specific date of the postoperative visit will also be communicated.

At each follow-up visit, the patient will directly visit the counselor’s office. Upon arrival, they will be provided with a blank sheet of paper containing the unique identification number assigned to them on the first postoperative day. Visual acuity testing will be conducted by a blinded optometrist, while slit lamp biomicroscopy will be performed by a blinded ophthalmologist. Before leaving the hospital, the patient will return the paper to the counselor, who will then enter the necessary information into the patient’s file. 

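### The last visual acuity assessment is set at day 30 in group 1 but anywhere in days 25 to 30 in group 2, so outcome timing can differ by arm

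*Protocol article*

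**What the plan says.** Three places in the protocol article give the arms different final visits.

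- **Abstract, Objective:** group 1 has two follow-ups, "one on day 7 and other on day 30"; group 2 has a single one in days 25 to 30.
- **Abstract, Methods:** the standard arm has three fixed days, "Patients in group 1 will be examined on day 1, day 7, and day 30". The deferred arm has a range for its last visit instead: "whereas patients in group 2 will be examined on day 1 and once between days 25 to 30".
- **Specific Objectives:** group 1 has visits "one on day 7 and the other on day 30"; group 2 has one "visit between day 25 and day 30".

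Study Design, Setting, and Participants is looser. Group 1 is to attend "at 1 week and 1 month postoperatively". For group 2 it reads: "In group 2, patients will be instructed to attend a follow-up visit at 1 month postoperatively only". No day range is attached to either.

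Nowhere is group 1 given a window, a common assessment day set, or the difference explained. The Background describes the earlier deferral study, from which the sample size takes its reference values, as having a visit at days 25 to 30 in both of its arms.

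Primary Outcome names visual acuity, in terms of improvement or stability over the four weeks of follow-up. The abstract says that the arms will be compared on best-corrected acuity.

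**The concern.** The arms should differ only in whether the 1-week visit takes place. If group 1 is measured on day 30 and group 2 on any day from 25 to 30, they also differ in how long the eye has had to settle before the outcome is taken. For group 2 this is the only scheduled acuity measurement after the day 1 examination, and for group 1 it is the last. It therefore necessarily feeds the primary comparison.

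Any average change in acuity between days 25 and 30 would then be counted as an effect of deferral. The planning difference is only 0.025, so a small drift could be a visible fraction of it. The study is described as a noninferiority design, so what is at stake is a comparison that partly reflects booking practice.

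**Working it through.** **Inputs from the article**
- Group 1 final visit: day 30. Group 2 final visit: days 25 to 30 (abstract, Specific Objectives).
- Difference d = 0.025, SD = 0.1125, 263 per group (Sample Size and Sampling Technique).
- Comparability is inferred if P>.05 (Results).

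**Inputs assumed**
- Group 2 visits fall evenly over days 25 to 30, and group 1 attends on day 30.
- Acuity changes by r per day in that interval, in the units of d. The article gives no such rate.

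**The plan's own figure.** The printed formula gives 2 × (1.96 + 1.645)² × (0.1125/0.025)² = 2 × 12.996 × 20.25 = 526.3 per group. The printed 263 is half of that. This is a separate matter on which the present point does not rest; 263 is used below only because it is the stated group size.

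**Step 1, timing gap.** Mean visit day in group 2 = (25 + 26 + 27 + 28 + 29 + 30)/6 = 27.5. Mean gap = 30 − 27.5 = 2.5 days. The largest possible gap is 30 − 25 = 5 days and the smallest is 0.

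**Step 2, shift in the arm difference.** Shift = gap × r.

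| r per day (assumed) | Shift, mean gap 2.5 days | Share of d | Shift, 5-day extreme | Share of d |
|---|---|---|---|---|
| 0 | 0 | 0% | 0 | 0% |
| 0.001 | 0.0025 | 10% | 0.005 | 20% |
| 0.002 | 0.005 | 20% | 0.010 | 40% |

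**Step 3, shift against sampling error.** SE = 0.1125 × √(2/263) = 0.0098. A shift of 0.0025 is 0.25 SE and a shift of 0.005 is 0.51 SE.

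**Step 4, consequence at the mean gap, with no true effect of deferral.**
- Under the P>.05 rule, the chance of a significant difference is Φ(shift/SE − 1.96) + Φ(−shift/SE − 1.96). It is 5.0% with no shift, 5.75% at 0.0025 and 8.0% at 0.005.
- If 0.025 is instead read as a noninferiority margin tested at one-sided 2.5%, power with the shift against group 2 is Φ((0.025 − shift)/SE − 1.96). It is 72% with no shift, 63% at 0.0025 and 53% at 0.005.

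**Step 5, with one common window used in the same way in both arms.** The scheduled gap is 0 days and the shift is 0 whatever r is.

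**The case against.** The strongest case against is that this may be no more than loose wording.

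- **One month for both arms.** The section with the operational detail instructs both arms alike, and one month is compatible with either day 30 or days 25 to 30. It is therefore not a flat contradiction. But without a day range it does not override three consistent statements of unequal timing.
- **Little room for drift.** Best correction takes uncorrected refractive error out of the comparison, and the Background names that as one of two main causes of poor outcome. The gap is at most 5 days. Acuity may well be stable by then, and the bias negligible. This stands; the documents do not settle it.
- **Direction.** If acuity is still improving, the shift works against group 2. In a noninferiority test that costs power and does not produce a false claim. This also stands. A gain in false claims would need acuity to fall in week 4, and nothing in the article suggests that.

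Three stronger readings are tempting but not supported.

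- A reader might infer that the bias cannot be removed afterwards. The schedules overlap at day 30, and visit day can vary within group 2, so restriction or adjustment is possible. It would be imperfect, because visit day is not randomised and is tied to arm.
- A reader might infer a bias as large as half of d. That needs 0.005 per day (2.5 × 0.005 = 0.0125). Continued over 30 days, this rate is 0.15, more than the SD of 0.1125, and the documents give no rate at all.
- A reader might take the primary outcome to be defined as acuity at the final visit. Primary Outcome speaks of the whole 4-week period. That the final visit carries the comparison is an inference from the schedule, though a strong one.

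**Conclusion.** The point holds as a scheduling asymmetry that should be removed, not as a demonstrated bias. As written in the abstract and the Specific Objectives, final assessment time can differ systematically by arm by 0 to 5 days. The mean of 2.5 days rests on an even spread in group 2 and day-30 attendance in group 1. The effect on the arm difference is unknown: nil if acuity is stable by day 25, and 10% to 20% of d at the illustrative 0.001 to 0.002 per day, with group 2 disadvantaged if acuity is still improving. The importance is modest, but correction before enrolment costs almost nothing, whereas adjustment afterwards would weaken the randomised comparison.

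**What to change.** Reconcile the abstract objective, the abstract methods, the Specific Objectives, and Study Design, Setting, and Participants so that both arms have one identical final-assessment window. Which window to use is for the sponsor to decide. Have the counselor book both arms across it in the same way. Name that visit as the time point of the primary comparison. Record the actual postoperative day of each assessment, and use it in a sensitivity analysis.

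The cost is a few words in four places and one booking instruction, with slightly more or less booking flexibility in one arm. No extra visit or additional patients are needed.

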**Results:**

The study is expected to be completed within 6 to 8 months from the start of the project. Data analysis and report writing will be carried out in a 2-month period. Best-corrected visual acuity will be compared between the 2 groups to determine if the MCID is achieved. The cost-effectiveness of the new approach will also be analyzed.

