### Sample Size and Sampling Technique

Sample size is calculated as follows: 2[Zα + Z1 – β] 2 × (sd2/d2) = 2 [1.96 + 1.645 ] 2 × [(0.1125)2/(0.025)2] = 263 for one group, where reference mean values for postoperative visual outcomes are taken from the study conducted by Deshpande et al [25]. The number of participants in intervention group will be 263 and the number of participants in the control (reference) group will be 263. We will use a random sampling technique and computer-generated random numbers to assign patients to the intervention or control group. We generated randomized numbers with a commonly used method [26]. The assignment will be done by the counsellor on the first postoperative day. The researchers will be masked as to randomization at all postoperative visits.

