### Primary Outcome

Visual acuity measurements serve as the most important primary outcome. This includes assessing the level of visual improvement or stability achieved by patients during the 4-week follow-up period. Visual acuity outcomes can provide insights into the effectiveness of deferring follow-up visits for achieving comparable visual outcomes to the standard practice of early postoperative visits.

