## Results

More than 526 participants will be enrolled in the study, with a minimum of 263 assigned to the intervention group (deferred follow-up visits) and a minimum of 263 to the comparison group (standard practice of early postoperative follow-up visits). The sample will have diverse demographics, ensuring a representative population.

Visual acuity measurements will be obtained for both groups during the follow-up period. We will be able to statistically compute whether the deferred follow-up visit group demonstrates comparable visual acuity outcomes to the comparison group. This will be inferred if there are no statistically significant differences between the two groups in terms of visual acuity outcomes (*P*>.05).

Among the participants in the deferred follow-up visit group, the number of patients who experience postoperative complications during the 4-week follow-up period will be compared with the group with the 1-week follow up visit.

We will also determine if participants in the deferred follow-up visit group report high levels of satisfaction with the extended recovery period and reduced travel burden. The number of participants who express that deferring follow-up visits provided them with convenience and comfort during the recovery phase will be mentioned.

We will determine if reduction in early postoperative visits allows health care providers to allocate their time and expertise more efficiently, focusing on patients with immediate needs or complex postoperative care requirements.

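### A noninferiority design with no stated margin: d = 0.025, an unnumbered Snellen MCID and P>.05 do not form one success criterion

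*Protocol article*

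**What the plan says.** - **Design** (Study Design, Setting, and Participants): "This will be a prospective, quantitative, experimental, noninferiority control study of health services use". No section gives a noninferiority margin.
- **Sizing** (Sample Size and Sampling Technique): the formula ends "0.1125)2/(0.025)2] = 263 for one group". The values 0.1125 and 0.025 carry no unit, and 0.025 is called neither a margin nor an MCID. The only source named is an earlier study: "where reference mean values for postoperative visual outcomes are taken from the study conducted by".
- **MCID** (abstract, Methods): "The minimum clinically important difference (MCID) in our study will be set according to the improvement in the Snellen visual acuity chart". No value follows, and the body of the article does not return to the MCID.
- **Use of the MCID** (abstract, Results): "Best-corrected visual acuity will be compared between the 2 groups to determine if the MCID is achieved".
- **Primary outcome** (Primary Outcome): visual acuity, with "This includes assessing the level of visual improvement or stability achieved by patients during the 4-week follow-up period". No threshold is given.
- **Decision rule in the body** (Results): comparability "This will be inferred if there are no statistically significant differences between the two groups in terms of visual acuity outcomes", with P>.05 as the criterion.

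**The concern.** A noninferiority trial needs one number: the largest deficit in the deferred group that would still be acceptable. That number should drive the sample size, and the confidence interval should be compared with it at the end. Here the sizing uses one number, the abstract refers to another that has no value yet, and the body uses a significance test that needs neither.

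The P>.05 rule is the only one that can be applied as printed, and it is not a noninferiority test. It rewards imprecision, because the smaller or noisier the trial, the larger the deficit that goes unnoticed. The MCID rule cannot be applied until a value is set. It is framed as improvement, whereas a margin is a tolerable difference between groups, and the article does not say whether reaching the MCID would count for or against deferral.

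At stake is the main conclusion. The same data could support deferral under one stated criterion and fail to support it under another.

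**Working it through.** **Inputs.** From Sample Size and Sampling Technique: SD 0.1125, d = 0.025, z values 1.96 and 1.645, and 263 per group. From Results in the body: the P>.05 rule. MCID values of 0.05 and 0.10 are assumptions on the same unstated scale as d, because the article gives none. A positive difference means that the deferred group is worse.

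**The plan's own figure.** 2 × (1.96 + 1.645)² × (0.1125/0.025)² = 2 × 12.996 × 20.25 = 526.3 per group. The printed 263 appears only without the leading 2 (12.996 × 20.25 = 263.2). This is a separate error. The figures below use 263 per group because that is the stated enrolment.

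**Precision.** SE = SD × √(2/n) = 0.1125 × √(2/263) = 0.00981. Half-width of the 95% CI = 1.96 × 0.00981 = 0.0192.

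**What each rule accepts.**
- P>.05: any observed difference below 0.0192 in absolute value.
- CI excludes a deficit of 0.025: observed deficit below 0.025 - 0.0192 = 0.0058.

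Observed deficits from about 0.006 to 0.019 therefore pass the first rule and fail the second.

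| Observed deficit | 95% CI | P | P>.05 rule | Excludes 0.025 | Excludes 0.05 (assumed) | Excludes 0.10 (assumed) |
|---|---|---|---|---|---|---|
| 0.005 | -0.014 to 0.024 | 0.61 | pass | yes | yes | yes |
| 0.010 | -0.009 to 0.029 | 0.31 | pass | no | yes | yes |
| 0.015 | -0.004 to 0.034 | 0.13 | pass | no | yes | yes |
| 0.030 | 0.011 to 0.049 | 0.002 | fail | no | yes | yes |

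The rows for 0.010 and 0.015 show the conflict using only numbers that the article prints. The row for 0.030 shows a further conflict that arises only if the MCID is later set at one of the assumed values.

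**Power at zero true difference, 263 per group.** Φ(margin/SE - 1.96):
- margin 0.025: Φ(2.548 - 1.96) = 0.722
- margin for 95% power: (1.96 + 1.645) × 0.00981 = 0.035

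**If the formula's own 526 per group were used.** SE = 0.00694 and half-width = 0.0136. The range of disagreement between P>.05 and a margin of 0.025 shrinks to 0.0114 (0.025 - 0.0136) to 0.0136, but does not vanish. A deficit of 0.020 (CI 0.006 to 0.034) would still fail at 0.025 and pass at an assumed 0.05.

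**The case against.** The strongest reply is that nothing here is shown to be incompatible. In a noninferiority trial the d of the sizing formula is ordinarily read as the margin, and the MCID might simply equal 0.025. The article is also condensed, and a full protocol or analysis plan may supply the number.

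Part of this stands. A missing MCID value in an abstract would not be a finding by itself, and the article does not show that the MCID differs from d. But the P>.05 rule is printed, and it disagrees with d = 0.025 whatever the MCID turns out to be. A later document could add a margin, yet the printed rule would still have to be withdrawn.

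Several stronger readings are tempting and should not be adopted:
- **That the MCID is used backwards.** A reader might infer this, since a deficit that reaches the MCID would count against deferral. But the sentence can also mean checking whether the difference reaches the MCID, with not reaching it as the favourable result. The direction is undefined rather than shown to be wrong.
- **That 0.025 is a quarter of a chart line.** This assumes logMAR. The article names only the Snellen chart and gives no scale.
- **That 72% power measures the harm of the undefined MCID.** It reflects the separate factor of 2 in the sizing.
- **That the primary outcome changes between sections.** The Primary Outcome text is a general description and can be read alongside the best-corrected acuity named in the abstract.
- **That the threshold will be picked after the data are seen.** The article uses the future tense throughout. The wording leaves this open but does not show it.

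**Conclusion.** The point holds in this form: the trial is declared noninferiority, no margin is stated, and no stated decision rule uses the 0.025 on which the trial was sized. Following the rule in the body would declare the groups comparable for observed deficits of about 0.006 to 0.019, although a deficit of 0.025 remains inside the confidence interval.

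This rests on the article's own SD and 263 per group, a normal approximation, and reading 0.025 as the deficit to be excluded. It does not depend on which acuity scale was used, provided that d and SD share it. The conflict at 0.05 or 0.10 is conditional on those assumed values. The matter should be settled before outcome data are unmasked, because it decides what the main conclusion means.

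**What to change.** 1. Name final-visit best-corrected visual acuity, on one stated scale, as the primary variable.
2. Fix one numeric noninferiority margin with a clinical justification before outcome data are unmasked, and say whether 0.025 is that margin.
3. Use the same number in the sample-size formula and in the decision rule: noninferiority is concluded if the 95% CI for the difference excludes a deficit as large as the margin. This rule replaces both the MCID wording in the abstract and the P>.05 wording in Results.
4. Restate the power that 263 per group gives at that margin.

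**Cost.** Mostly wording. If 0.025 is kept, the stated power becomes less favourable: about 72% with 263 per group. No extra enrolment is needed if that power is reported as it is. Holding 95% power at 0.025 would take 527 per group (526.3 from the printed formula; 527 with unrounded z values). With 263 per group, 95% power is reached only for margins of about 0.035 or more, and a wider margin should be chosen on clinical grounds rather than to fit the enrolment.

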**Results:**

The study is expected to be completed within 6 to 8 months from the start of the project. Data analysis and report writing will be carried out in a 2-month period. Best-corrected visual acuity will be compared between the 2 groups to determine if the MCID is achieved. The cost-effectiveness of the new approach will also be analyzed.

**Conclusions:**

We aim to conclude that we can safely defer the 1-week postoperative follow-up visit in patients undergoing uncomplicated cataract surgery and that, moreover, we can reduce the patient load at the hospital and decrease patient expenses by decreasing the frequency of hospital visits.

**International Registered Report Identifier (IRRID):**

PRR1-10.2196/48616

## Introduction

### Background

Cataract is the leading cause of blindness and visual impairment in lower- and middle-income countries [1,2]. Surgery is the only available treatment that is highly cost-effective and capable of significantly improving visual function [3,4]. Cataract surgery often achieves an excellent visual outcome with low rates of complication [5,6]. Routine examination after cataract surgery, including a refraction test a few weeks after surgery, is mandatory in most hospitals [7,8].

Limburg et al [9] investigated the benefits of postoperative follow-up in India and concluded that visual acuity at hospital discharge was not representative of visual acuity several weeks after surgery [10]. However, a study by Congdon et al [11] concluded that early vision assessment of all patients and a follow-up assessment only for patients who return to the clinic without prompting were adequate to ensure the quality of cataract surgical services. This is again countered by a study by Gupta et al [12], who presented evidence of substantial changes between visual acuity on the first postoperative day and at subsequent follow-up. Postoperative complications and uncorrected refractive errors are 2 major issues that lead to poor visual outcomes [5,13-16]. Both issues can be wholly addressed by promoting and ensuring postoperative follow-up at the designated time [17-20]. As per the National Programme of Control of Blindness, Vision 2020: Right to Sight, the recommended postoperative follow‑up visit schedule is a first follow‑up on the first postoperative day by the surgeon (mandatory), a second follow‑up between day 7 and day 10, and a third follow‑up (with refractive correction) between day 30 and day 45 [21]. Saeed et al [22] and Tinley et al [23] concluded that postoperative follow‑up visits can be safely deferred up to 2 weeks after cataract surgery, thereby enhancing the efficiency of day care units. Meltzer et al [24] performed a study using data from the PRECOG (Prospective Review of Early Cataract Outcomes and Grading) trial and reported that visual acuity immediately after cataract surgery was highly correlated with visual acuity after 40 days, suggesting that for the purposes of quality assessment, follow‑up of all patients is not needed. A study by Deshpande et al [25] concluded that visual outcomes after uneventful cataract surgery were comparable between patients followed up on days 3 to 7 and days 25 to 30 in comparison to patients directly followed up on days 25 to 30. Additionally, it was observed that the first follow‑up visit could be safely deferred until 4 weeks after uneventful cataract surgery, including phacoemulsification or small-incision cataract surgery (SICS), in patients with no preexisting ocular or systemic comorbidity [25]. The purpose of this study is to evaluate, from a safety perspective, altering the standard postoperative management guidelines after cataract surgery so that the first follow‑up visit at 1 week is deferred in patients with no significant preexisting ocular or systemic comorbidity and no intraoperative surgical complications or immediate postoperative complications at the time of discharge from the hospital.
